### **Signs of Improvement:**

In absence of complications, within 2 days of initiation of treatment there should be signs of improvement  
i ) breathing rate within normal limit; ii) absence of the lower chest wall in-drawing; iii) less to no fever; iv) improved ability to eat and drink; and v) better oxygen saturation without assistance.

### **Discharge criteria**

- Respiratory distress has resolved
- Oxygen saturation > 90%
- Feeding well
- Able to take oral medication or have completed a course of parenteral antibiotics
- The parents understand the signs of pneumonia, risk factors and when to return

### **Laboratory investigations:**

No additional laboratory investigations will be required to perform this study. Routine management of severe pneumonia will be followed as per the existing pneumonia guideline practiced in Dhaka Hospital. The patients with suspected sepsis will be investigated for source of infection by CBC, Blood culture and chest X-ray. Any patient with severe acute malnutrition (SAM) and cough and/or fast breathing will be investigated for chest X ray and CBC. There will be no incurrence of hospitalization cost to conduct the research.

### **Respiratory ward Infrastructure:**

An independent acute respiratory infection treatment unit was established right at the entrance to the hospital, and started functioning on 6 September, 2009. Patients reporting to Dhaka Hospital were rapidly screened for

respiratory symptoms such as fever, cough, myalgia, headache, chills, fatigue, running nose, sore throat, rapid breathing and difficulty in breathing. Patients with these symptoms were referred to the respiratory triage where they were assessed following the hospital guidelines and relevant information was entered into the hospital's electronic database. Patients with any form of pneumonia (non-severe, severe, and very severe), bronchiolitis, asthma, bronchitis, pleural effusion, empyema, lung abscess, tuberculosis, and any other common respiratory problems are admitted in the ward. Others were referred to the usual diarrhoea triage of the hospital. Sufficient staff provide 24 hour cover from all cadres (doctors, nurses, health workers and auxiliary staff). This facility was provided with all necessary supplies including a portable X-ray machine, Ambu bags, large oxygen cylinders, pulse oxymeters, disposable gloves, disinfectants and medication (e.g. antibiotics and other medicines). Pulse oxymetry is routinely performed to evaluate arterial oxygen saturation, and additional tests were performed if there were clinical indications. Vital signs were monitored, and stool and urine output was measured and recorded 8 hourly. Therapy is decided on the basis of clinical evaluation, results of the laboratory tests, and the hospital guidelines for management of respective respiratory illness.

### **Ambulatory care Unit:**

This is a new set up in Dhaka Hospital and the facility is used to reduce patient hospital stay as well as nosocomial infection rate. This facility is only offered to the patients who have recovered from the acute illness and showing signs of improvement. The patients who live in Dhaka city and able to return to Dhaka hospital are requested to come to receive injectable drugs every morning. Drugs will be provided from hospital free of cost. The total procedure will take less than one hour and patient can go home afterward. By this care the antibiotic course will be completed and hospitalization cost can be minimized.

### **Sample Size Calculation and Outcome (Primary and Secondary) Variable(s)**

Clearly mention your assumptions. List the power and precision desired. Describe the optimal conditions to attain the sample size. Justify the sample size that is deemed sufficient to achieve the specific aims.

### **Sample size calculation:**

[For two-sample comparison of proportion (non-inferiority)]

Null hypothesis:  $p_2 - p_1 \leq \delta$  (inferior), where:  $p_i$  (entered in command) is the overall proportion of participants expect to experience the outcome if the treatments are non-inferior, and delta is the smallest change in proportions between groups ( $p_2 - p_1$ ) which would still be clinically important.

Assumptions:

power = 0.8; alpha = 0.025 (one-sided);  $p_i = 0.50$ ; delta = 0.16

Estimated required sample size (per group) = 154,

Total sample is 308

**Primary Outcome:** Treatment failure which is defined by the persistence of danger signs of severe pneumonia for >48 hours or deterioration within 24 hours of initiation of therapy (development of new danger signs or clinical signs of respiratory failure, or development of severe sepsis/meningitis, or, radiological deterioration).

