**Treatment failure:**

Treatment failure is defined by the persistence of danger signs of severe pneumonia for >48 hours or deterioration within 24 hours of initiation of therapy or if child needs mechanical ventilation, dies at any time during hospital stay or left the hospital against medical advice.

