**Outcome measures/variables:**

- Primary outcome is treatment failure
- Secondary outcome (i) time of resolution or recovery from pneumonia (ii) danger sign (iii) total hospitalization period for pneumonia

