**Secondary objectives:**

To compare time to resolution of danger signs of pneumonia, length of hospital stay, mortality rate, rate of complication requiring mechanical ventilation, and rate of multiorgan or renal or cardiac failure between the two treatment groups.

**Primary Outcome:** Treatment failure which is defined by the persistence of danger signs of severe pneumonia for >48 hours or deterioration within 24 hours of initiation of therapy (development of new danger signs or clinical signs of respiratory failure, or development of severe sepsis/meningitis, or, radiological deterioration).

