### **Study Interventions:**

Children between 2 months to 59 months with severe pneumonia will be studied to evaluate the proportions of treatment failure in two different arms.

We will use sealed envelopes to randomly assign the children to either treatment arms. In first arm children will receive 2 daily doses of parenteral Amoxicillin and single daily dose of parenteral Gentamicin; and in 2nd arm, children will receive 4 daily doses of parenteral Ampicillin and single daily dose of parenteral Gentamicin. After 72 hours of treatment, injection Amoxicillin and injection Ampicillin will be replaced with oral Amoxicillin but injection gentamicin will be continued for total 5 days in once daily dose. During this time patient will be suggested to discharge from hospital and attend to Ambulatory care unit for getting once daily dose of injection Gentamicin. Both the treatment arm will continue for 5 days.

During the study period, children in both study arms will also receive standardized hospital management for diarrhoea and malnutrition (*Annex 2,3*).

“Treatment failure” will be standardized, based on clinical and monitoring data. Treatment failure is defined by the persistence of danger signs of severe pneumonia for >48 hours or deterioration within 24 hours of initiation of therapy or if child needs mechanical ventilation, dies at any time during hospital stay or left the hospital against medical advice.

During the study period any child from either study group who develops the features of “clinical failure” (any two of three criteria in the definition below) will be managed according to best practice in the clinical context. If children fail any arm of treatment, they should be rescued with second line antibiotic regimen, which is injection ceftriaxone and injection levofloxacin. Hypoxia will be managed by B-CPAP or humidified high flow air / O2 mix at 2 l/kg/min through nasal cannula.

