### **Intention to treat (ITT) analysis:**

It is essential to mention that the children who will be “absconded” from our study after randomization due to any reason will also be included in our primary analysis and will be considered them as INTENTION TO TREAT (ITT) ANALYSIS. Thus, ITT analysis should be, any child who, after randomization fulfil any following criteria:

1. Criteria for treatment failure as defined in the proposal
2. Receives intubation and / or mechanical ventilation
3. Dies during hospitalization
4. Left against medical advice

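### The primary outcome is defined in two ways: one counts ventilation, in-hospital death and leaving against advice as failure, the other does not, and the ITT section only partly settles it

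*Protocol*

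**What the plan says.** **Narrow form.** Under Sample size calculation, the paragraph labelled Primary Outcome defines treatment failure as "persistence of danger signs of severe pneumonia for >48 hours or deterioration within 24 hours of initiation of therapy (development of new danger signs", with more criteria following. The same paragraph stands under Specific Aims. Both spell deterioration out in full as "development of new danger signs or clinical signs of respiratory failure, or development of severe sepsis/meningitis, or, radiological deterioration". Each is followed by a list of secondary outcomes that includes death in hospital.

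**Wide form.** The Project Summary, under Treatment failure, has the same two components without criteria for deterioration, and adds failure "if child needs mechanical ventilation, dies at any time during hospital stay or left the hospital against medical advice". The summary's outcome list then says "Primary outcome is treatment failure". Study Interventions repeats the wide form: "or if child needs mechanical ventilation, dies at any time during hospital stay or left the hospital against medical advice".

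**ITT section.** Children who abscond after randomisation are to be in the primary analysis. Four criteria follow. The first is treatment failure as the proposal defines it. The second is "Receives intubation and / or mechanical ventilation". The third and fourth are death in hospital and leaving against advice.

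**Case record form (Annex 4).** Item 152 codes the final outcome and includes unimproved but discharged on request, DORB, and absconded. Item 153 is a single treatment-failure entry with no definition attached.

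**The concern.** A non-inferiority trial needs one meaning for its primary endpoint before anyone sees outcome data. Here two current texts, each presented as the primary outcome, disagree on whether ventilation, death and leaving against advice count. The trial is open label, so staff and families know the arm, and that knowledge can influence who leaves. If the definition is still open at analysis, it can be settled with the results in view. The gap over absconders adds a second choice of the same kind, because the analyst must decide which outcome codes amount to leaving against advice.

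**Working it through.** **Step 1: the definitions side by side.**

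| Event | Project Summary; Study Interventions | Specific Aims; Sample size calculation | ITT section |
|---|---|---|---|
| Danger signs beyond 48 h | failure | failure | through item 1 |
| Deterioration within 24 h | failure, no criteria | failure, four criteria | through item 1 |
| Mechanical ventilation | failure | not listed | item 2, separate |
| Death in hospital | failure | not listed; death is a secondary outcome | item 3, separate |
| Leaving against advice | failure | not listed | item 4, separate |
| Absconding | not named | not named | in the primary analysis, but in none of the four items |

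**Step 2: a child on whom they differ.** Suppose danger signs clear by 40 h and there is no deterioration in the first 24 h. The child is then ventilated at 60 h, dies on day 4, or leaves against advice on day 3. Under the wide form this child is a failure. Under the narrow form neither component is met, so the child is not a failure. The forms agree on a child with respiratory failure in the first 24 h.

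**Step 3: the cross-references.** The primary hypothesis, under Hypothesis to be tested, refers back to a definition given above; the only one before it is the wide form in the Project Summary. The Outcome variables section also refers to a definition above; the nearest one there is the narrow form under Sample size calculation. The hypothesis and the outcome section therefore lead to different endpoints.

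**Step 4: what the ITT section implies.** Write N for the narrow set, W for the wide set, and V, D, L for ventilation, death and leaving, so that W = N + V + D + L.
- If item 1 means N, the four items give N + V + D + L = W.
- If item 1 means W, items 2 to 4 add nothing and the result is again W.

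Either way the primary analysis counts the wide set. One small wording difference remains: the wide form speaks of needing ventilation, and item 2 of receiving it.

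**Step 5: does the sample size depend on this?** Inputs from Sample size calculation: failure proportion 0.50 in both groups, margin 0.16, one-sided alpha 0.025, power 0.80, equal groups.

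n = (1.960 + 0.842)² × 2 × 0.50 × 0.50 / 0.16² = 7.849 × 0.50 / 0.0256 = 153.3, so 154 per group.

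This matches the protocol; power at 154 is 0.802. A proportion of 0.50 gives the largest variance, so with equal rates in both arms no move in either direction raises n. As an illustration only, assume that a further 2 to 15 percentage points fail only under the wide form. From 0.50 the rate becomes 0.52 to 0.65, the required n is 154 falling to 140, and power at 154 is 0.80 to 0.84.

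**The case against.** The strongest reply is that the ITT section already decides the matter. It governs the primary analysis, and step 4 shows that its four items give the wide set whichever definition item 1 means. That stands as a pointer to the intended reading. It does not remove the conflict: two paragraphs headed Primary Outcome still say otherwise, death still sits below them as a secondary outcome, and the ITT section treats the three events as additional to treatment failure as defined.

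A reader might infer more than the documents support:

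- *That the primary analysis will score deaths as successes.* This follows only if the narrow paragraphs are read without the ITT section.
- *That the wide form drops deterioration.* It keeps deterioration within 24 h and lacks only the criteria.
- *That a child who leaves on day 1 is a success under the narrow form.* Persistence beyond 48 h is then unobserved, so the status is undetermined.
- *That absconders are left out.* They are expressly in the primary analysis; what is missing is how they are classified.
- *That a known number of children change status.* No leaving rate is given. An assumed 10% would be about 15 of 154 per arm, and only as an upper bound, because leavers who already met a narrow criterion do not move.
- *That counting leavers as failures is what favours non-inferiority.* If a share L leaves in both arms, a 16-point difference among stayers shrinks to (1 − L) × 16 points whether leavers are coded as failures or as non-failures. With 0.50 v 0.66 among stayers and L assumed at 5%, 10% and 20%, the chance of declaring non-inferiority is 3.5%, 4.8% and 8.7% coded as failures, and 3.5%, 4.7% and 8.2% coded as non-failures. The inflation comes from leaving itself, so it is not evidence about this conflict.

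**Conclusion.** The protocol is wrong as written: it states two incompatible primary outcomes in current text, with cross-references that lead to different ones. This rests on reading the sections together and needs no assumed figure. The ITT section favours the wide set but does not make it the definition, and neither its four items nor the case record form codes say how absconders are classified.

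The consequence is an endpoint that can be chosen after results are seen in an open-label trial. It is not a wrong sample size: 154 per group reproduces and would not rise under equal rates in the two arms. The number of children who would change status cannot be derived from the documents. The point must be settled before outcome data are examined.

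**What to change.** Reconcile the Project Summary (Treatment failure), Specific Aims, Study Interventions, Sample size calculation, Outcome variables and ITT sections into one analysis definition of the primary outcome, before data are examined. The reading that the protocol's own primary analysis supports is the ITT section's set, with the deterioration criteria given in Specific Aims and Sample size calculation.

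State how the item 152 codes (discharged on request, DORB, absconded) map to that definition, and tie item 153 to it. Add one sensitivity analysis that classifies leavers by their last observed clinical status.

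This concerns the analysis endpoint only. Study Interventions also uses failure to trigger rescue treatment, and refers to a clinical failure rule whose definition is said to follow but does not. The investigators must reconcile that wording; no clinical rule is proposed here.

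The cost is protocol wording, a code mapping and one extra analysis. No additional children are needed.

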### **Secondary outcomes:**

1. Time to resolution of danger signs of severe pneumonia
2. Length of hospital stay
3. Death during hospitalization

### ***Outcome variables***

1. The primary outcome variable will be treatment failure (see definition above).
2. The secondary outcome variables will be:
  - I. Time to resolution of danger signs of severe pneumonia
  - II. Length of hospital stay
  - III. Death during hospitalization

### **Data Analysis**

Describe plans for data analysis, including stratification by sex, gender and diversity. Indicate whether data will be analysed by the investigators themselves or by other professionals. Specify what statistical software packages will be used and if the study is blinded, when the code will be opened. For clinical trials, indicate if interim data analysis will be required to determine further course of the study.

### **Data analysis plan:**

Data analyses will be performed using the SPSS, version 20.0 Windows, (SPSS, Chicago, IL) and Epi Info (version 7.0, USD, Stone Mountain, GA). Statistical analyses include descriptive as well as analytical methods. Intention to treat (ITT) analysis will be performed. For categorical variable, the significance of differences will be evaluated comparing Amoxicillin arm with Ampicillin arm by chi-square test or Fisher exact test as appropriate. For continuous variables, for normally distributed data the differences of means will be compared by Student's t-test and for not normally distributed data Mann-Whitney test will be used. A p-value < 0.05 will be considered statistically significant. Strength of association will be determined by calculating relative risks and their 95% confidence intervals.

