**Description of the Research Project**

**Hypothesis to be tested:**

In a hypothesis testing research proposal, briefly mention the hypothesis to be tested and provide the scientific basis of the hypothesis, critically examining the observations leading to the formulation of the hypothesis.

Does this research proposal involve testing of hypothesis: ☐ No ☒ Yes (describe below)

On the basis of the above background, our primary hypothesis is that:

Treatment failure (defined above) with two doses of injectable Amoxicillin plus single dose of injectable Gentamicin will be comparable with four doses of injectable Ampicillin plus single dose of injectable Gentamicin in the management of children under five hospitalized for WHO classified severe pneumonia.

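### The trial is sized for non-inferiority with a 16-point margin, but its only stated comparison is a test of difference with a relative risk, and nothing is held against the margin

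*Protocol*

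**What the plan says.** **Sample size.** The Protocol's section on sample size calculation heads the calculation "For two-sample comparison of proportion (non-inferiority". The inputs are power 0.8, one-sided alpha 0.025, an expected proportion of 0.50 and delta 0.16. Delta "is the smallest change in proportions between groups" that would still matter clinically, so it is an absolute risk difference. The result is given as "Estimated required sample size (per group) = 154", 308 in all.

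**Hypothesis.** The section on the hypothesis to be tested says that failure on the amoxicillin regimen "will be comparable with four doses of injectable Ampicillin plus single dose of injectable Gentamicin". The Project Summary says that failure on amoxicillin will not exceed that on ampicillin. Both are non-inferiority ideas, and the primary outcome, treatment failure, is a yes/no variable.

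**Analysis.** The Data analysis plan says that for categorical variables "the significance of differences will be evaluated comparing Amoxicillin arm with Ampicillin arm by chi-square test or Fisher exact test as appropriate", with p < 0.05 counted as significant. It adds: "Strength of association will be determined by calculating relative risks and their 95% confidence intervals". The Protocol describes no other comparison of the arms. The section on intention to treat adds only rules on who is included and who counts as a failure. The margin, a confidence interval for the risk difference, a one-sided test and a non-inferiority decision rule appear nowhere outside the sample size section.

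**The concern.** The named analysis differs from the design in two ways.

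- **Null hypothesis.** A chi-square or Fisher test takes equality as its null. The design takes an excess of 16 points as its null. Rejecting equality does not confirm the hypothesis, and failing to reject it shows only that a difference was not detected.
- **Scale.** The margin is a difference in proportions and the planned effect measure is a ratio. No relative-risk margin is given, so the relative-risk interval cannot be judged.

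At stake is the trial's main conclusion: whether a regimen with fewer injections is acceptable in children with severe pneumonia. If a non-significant p-value is reported as comparability, the 2.5% error control built into the sample size does not apply to that claim.

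**Working it through.** **Inputs** (Protocol, sample size calculation): p = 0.50, margin 0.16, one-sided alpha 0.025 (z = 1.960), power 0.80 (z = 0.842), n = 154 per arm. From the Data analysis plan: significance at p < 0.05, taken as two-sided because the sidedness is not stated.

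**1. The Protocol's own figure.**
n = 2 × 0.50 × 0.50 × (1.960 + 0.842)² / 0.16² = 153.3, rounded up to 154 per arm. It reproduces as a non-inferiority size. The superiority formula for 50% against 66% gives 149, so 154 is not a superiority size under another name.

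**2. How the two rules behave at 154 per arm.** Exact enumeration of two independent binomials. Rule A: the uncorrected two-sided 5% chi-square is non-significant. Rule B: the upper limit of the two-sided 95% Wald interval for the risk difference (amoxicillin minus ampicillin) is below 0.16.

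| True failure, amoxicillin v ampicillin | A: not significant | B: non-inferior | A met but B not met |
|---|---|---|---|
| 50% v 50% | 95.4% | 80.4% | 17.3% |
| 60% v 50% | 58.7% | 18.2% | 40.6% |
| 66% v 50% (at the margin) | 18.4% | 2.3% | 16.1% |

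A normal approximation agrees. At 66% v 50% the pooled standard error is √(2 × 0.58 × 0.42 / 154) = 0.0562 and the unpooled one is √((0.66 × 0.34 + 0.50 × 0.50) / 154) = 0.0555. Chi-square power is Φ((0.16 − 1.96 × 0.0562) / 0.0555) = 0.815, so non-significance has probability 0.185. Rule B passes with probability Φ(−1.96) = 0.025.

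If Rule A were used to claim comparability, the error at the margin would be 18.4 / 2.5, about seven times the planned level.

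**3. Sensitivity to the failure rate.** Lower ampicillin rates are illustrative assumptions; the Protocol gives only 50%. At the margin, Rule A passes in 11.6% of trials at 36% v 20% and in 3.65% at 26% v 10%. Rule B passes in 2.5% and 2.7%. The excess error is large at the Protocol's own rate and shrinks as failure becomes rarer.

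**4. One possible result.** Failures of 92/154 v 77/154, or 59.7% v 50.0%:
- Chi-square p = 0.086, not significant.
- Risk difference 9.7 points, 95% interval −1.3 to 20.8. The upper limit exceeds 16, so non-inferiority is not shown.
- Relative risk 1.19, 95% interval 0.97 to 1.47, with no stated limit to compare it with.

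**5. Why the relative risk cannot stand in for the margin.** A 16-point excess is a relative risk of (0.50 + 0.16) / 0.50 = 1.32 at 50% failure on ampicillin, 1.53 at 30%, 1.80 at 20% and 2.60 at 10%. The margin does not translate into one relative risk.

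**The case against.** - **Detail for a separate analysis plan.** The Data analysis plan is generic text for categorical variables and does not name the primary analysis. A separate statistical analysis plan, not seen here, might hold the margin-based test. This limits the claim to what the Protocol states. It does not remove the defect, because the Protocol names a test, a threshold and an effect measure that cover treatment failure and do not fit its own hypothesis. A later plan would have to override that text.
- **The decision rule is inferred.** The Protocol does not say that a non-significant p-value will be read as comparable. This stands, and the 18.4% is conditional on that reading. But the Protocol gives no other way to reach its hypothesis.
- **The 60% v 50% case is not an error.** This stands. Ten points lies inside the 16-point margin, so by the Protocol's own standard the regimen is non-inferior there. That row shows how often the rules disagree, not a false-conclusion rate.
- **Superiority test is not the Protocol's term.** True; it speaks only of differences. Nor do the error levels conflict in themselves, since a two-sided 95% interval corresponds to one-sided 0.025. The conflict lies in the null and the scale.

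**Conclusion.** The concern holds. The sample size is arithmetically correct for non-inferiority, but the only comparison the Protocol states cannot demonstrate non-inferiority, and no margin-based test is given. If non-significance were taken as comparability, a regimen worse by exactly the full margin would pass in 18.4% of trials instead of about 2.5%. That figure assumes 154 analysed per arm, 50% failure on ampicillin, an uncorrected chi-square at two-sided 5%, and the inferred reading of p. The mismatch itself depends on none of these. It governs the primary conclusion and should be corrected before the data are analysed.

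**What to change.** In the Data analysis plan, state that the primary analysis is the difference in treatment-failure proportions, amoxicillin minus ampicillin, with a two-sided 95% confidence interval by a named method (for example Newcombe or Miettinen-Nurminen). State that non-inferiority is concluded only if the upper limit is below +0.16. Keep the chi-square or Fisher p-value and the relative risk as secondary description, and say that p of 0.05 or more is not evidence of comparability.

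Two related texts should be settled in the same edit:

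- The sample size section does not say which arm is p1 and which is p2, and it labels a difference at or below delta as inferior. If p is the failure proportion and p2 the amoxicillin arm, that direction is reversed.
- The definition of treatment failure under Study Interventions includes ventilation, death and leaving against medical advice. The Primary Outcome definition does not list them, though the intention-to-treat section counts them. The tested quantity needs one definition.

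The cost is wording. No patients or data are added: the interval matches the one-sided 0.025 already assumed, and 154 per arm gives 80.4% power at 50% failure in both arms.

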**Physical examinations:**

54. Weight:   kg

Height/length:   cm

55. Z- score against weight for length/height: -----.

Z- score against weight for Age: -----.

56. MUAC : ----- cm

57. Temperature (axilla):

58. Heart rate:  bpm

59. Respiratory rate:  bpm

(at rest ,when not crying or coughing):

60. BP: \_\_\_\_/\_\_\_\_ mmHg

61. Capillary refill time : \_\_\_\_ seconds

62. Skin rash: 1=yes, 2=No ☐

63. Characteristics of the skin rash on admission ☐  
1=macular,2= papular,3=maculo-papular,4=petichieal,  
5=purpuric, 6= scaly, 7= urticarial, 8=others

64. Pedal oedema: 1=0,2=+, 3=++ , 4=+++ ☐

65. Pallor: 1=0,2=+, 3=++ ,4=+++ ☐

66. Eye discharge: 1=yes,2=No ☐

67. Nasal discharge: 1=yes,2=No ☐

68. Ear discharge: Right 1=yes,2=No ☐

Left 1=yes,2=No ☐

69.ASOM: Right 1=yes,2=No ☐

Left 1=yes,2=No ☐

70. Oral thrush: 1=yes,2=No ☐

71. Lymphadenopathy: 1=yes,2=No ☐

72. If Yes, generalized 1=yes,2=No ☐

73. If generalized lymphadenopathy: symmetrical node enlargement >2cm in at least two different anatomical sites 1=yes,2=No ☐

74. Digital clubbing: 1=yes,2=No ☐

75. Parotid swelling: 1=yes,2=No ☐

Respiratory findings:

76. Lower chest wall indrawing 1=yes,2=No ☐
77. Nasal flaring 1=yes,2=No ☐
78. Central cyanosis 1=yes ,2=No ☐
79. Grunting 1=yes ,2=No ☐
80. Head nodding 1=yes ,2=No ☐
81. Clear chest 1=yes ,2=No ☐
82. Crackles 1=yes,2=No ☐
83. Wheeze/Ronchi 1=yes,2=No ☐
84. Bronchial breath sounds 1=yes,2=No ☐
- [figure not shown]

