**89. Additional information on admission:**

☐

1=umbilical hernia , 2=Visual impairment or hearing loss, 3=others

90. Oxygen saturation on admission in air \_\_\_\_\_ %

91. PH on admission

|  |  |  |
|--|--|--|
|  |  |  |
|--|--|--|

92. PCO2 on admission

|  |  |
|--|--|
|  |  |
|--|--|

93. PO2 on admission

|  |  |
|--|--|
|  |  |
|--|--|

94. Base excess on admission

|  |  |
|--|--|
|  |  |
|--|--|

95. TCO2 on admission

|  |  |
|--|--|
|  |  |
|--|--|

96. HCO3 on admission

|  |  |
|--|--|
|  |  |
|--|--|

97. Random blood sugar : \_\_\_\_\_.\_\_\_\_\_ mmol/L

|  |
|--|
|  |
|--|

98. Main clinical diagnosis:

- 1. Very severe pneumonia
- 2. Very severe pneumonia with sepsis
- 3. very sever pneumonia withsevere sepsis
- 4. very sever pneumonia with septic shock
- 5. Other

Physician's initials: \_\_\_\_\_

Date: \_\_\_\_/\_\_\_\_/\_\_\_\_

---

*Principal investigator will complete final diagnosis according to study codes:*

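### Treatment failure is assigned only an unadjusted test although age, nutritional Z-score and admission SpO2 are already collected; the test is valid but may give up some precision

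*Protocol*

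**What the plan says.** The Data analysis plan gives one rule for all categorical variables: "the significance of differences will be evaluated comparing Amoxicillin arm with Ampicillin arm by chi-square test or Fisher exact test as appropriate". It adds relative risks with 95% confidence intervals and a 0.05 significance threshold. Treatment failure, the primary outcome, is binary and gets no rule of its own, so this one governs it. The Advanced data analysis plan adds only a cost analysis. No adjusted or stratified analysis of a clinical outcome appears in the protocol.

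On allocation, Study Interventions says "We will use sealed envelopes to randomly assign the children" to the two arms. It names no stratification factors and does not say whether allocation is simple or blocked.

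The sample size section is headed "For two-sample comparison of proportion (non-inferiority") and states "power = 0.8; alpha = 0.025 (one-sided"), an assumed failure proportion of 0.50, a delta of 0.16, and "Estimated required sample size (per group) = 154".

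The case record form (Annex 4) collects age (item 6), "Z- score against weight for length/height" (item 55) and "Oxygen saturation on admission in air" (item 90).

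**The concern.** In a randomised trial, adjusting for baseline values that predict the outcome removes the part of the between-arm noise that those values explain. The interval around the treatment difference becomes narrower with no extra children and no extra data.

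The protocol itself treats low oxygen saturation and severe malnutrition as markers of severity. Annex 1 uses saturation below 90% to define severe pneumonia and classes any pneumonia with severe malnutrition as severe. The section on monitoring asks for special attention to malnourished children. Age, Z-score and SpO2 are therefore natural candidates.

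The sample size meets its power target by a fraction of a percentage point at the assumed 50% failure rate. The Eligibility Criteria section shows that the investigators care about power, since it gives dilution of power as a reason for tighter entry criteria. Adjustment serves the same aim. Because the protocol names the unadjusted method, this is a choice it has made and not a detail it leaves open.

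**Working it through.** **Inputs from the protocol (Sample size calculation).** Failure proportion p = 0.50 in both arms; margin 0.16 on the risk difference; one-sided alpha 0.025; power 0.80; 154 per group.

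**Input that the protocol does not give.** R², the share of outcome variance explained by the baseline values. It is an assumption here, shown over the range 0 to 0.20.

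**Step 1: reproduce the stated size.**

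n per group = 2p(1 − p)(1.960 + 0.842)² / 0.16² = 0.5 × 7.849 / 0.0256 = 153.3, rounded up to 154. The stated figure reproduces.

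**Step 2: power and precision without adjustment.**

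SE = √(0.5/154) = 0.0570. Power = Φ(0.16/0.0570 − 1.960) = 80.2%. The 95% half-width is 1.960 × 0.0570 = 11.2 percentage points.

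**Step 3: with adjustment.** The variance is multiplied by (1 − R²):

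Power = Φ(0.16/√(0.5(1 − R²)/154) − 1.960); equivalent unadjusted size = 154/(1 − R²).

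| Assumed R² | Power at 154 per group | 95% half-width (points) | Equivalent unadjusted n per group |
|---|---|---|---|
| 0 | 80.2% | 11.2 | 154 |
| 0.02 | 81.0% | 11.1 | 157 |
| 0.05 | 82.1% | 10.9 | 162 |
| 0.10 | 84.1% | 10.6 | 171 |
| 0.15 | 86.1% | 10.3 | 181 |
| 0.20 | 88.1% | 10.0 | 192 |

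**Step 4: check by simulation.** 154 per arm, about 50% failure, three assumed standard-normal baseline values with equal effects, linear regression with robust standard errors, 3,000 runs per setting. The Monte Carlo standard error of each power is about √(0.8 × 0.2/3000) = 0.7 points.

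| R² in the simulated data | Variance ratio, adjusted/unadjusted | Power unadjusted | Power adjusted |
|---|---|---|---|
| 0 | 1.005 | 81.6% | 80.9% |
| 0.028 | 0.980 | 79.4% | 80.6% |
| 0.060 | 0.937 | 80.6% | 82.6% |
| 0.098 | 0.923 | 80.7% | 83.7% |
| 0.139 | 0.849 | 79.0% | 85.2% |

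The simulation agrees with the closed form. Adjusting for values with no predictive strength costs essentially nothing at this size.

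**Step 5: lower failure rates.** With 154 per group and margin 0.16, replace 0.5 by 2p(1 − p).

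| True failure proportion | Power, R² = 0 | Power, R² = 0.10 |
|---|---|---|
| 0.30 | 86.5% | 89.8% |
| 0.20 | 93.9% | 95.9% |

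At p = 0.20 the half-width is 1.960 × √(0.32/154) = 8.9 points without adjustment and 8.9 × √0.9 = 8.5 points at R² = 0.10. There the benefit is mainly a tighter estimate.

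**The case against.** The strongest case against is that nothing here is an error. An unadjusted comparison in a randomised trial is valid, and covariates are often chosen in the SAP. The stated size meets its 80% target at p = 0.50, the proportion with the largest variance, so power is higher at any other true rate. Every figure for the gain rests on an assumed R². There are also reasons to expect a small one. Entry requires at least two severity features, and respiratory failure and hypercapnia are excluded, so the range of severity is narrowed. In the Project Summary and Study Interventions, failure also includes leaving against medical advice, which admission SpO2 or Z-score need not predict. Finally, the protocol does not show that any of the three values predicts failure.

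Most of this stands, and it limits the size of the point. It does not remove it. The protocol has named the unadjusted method, adjustment with weak predictors costs almost nothing, and the values are collected anyway.

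Four stronger readings are tempting and are not supported:

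- A reader might infer that randomisation is simple and unstratified. The protocol is silent on this; it states no stratification, which is not the same as stating that there is none.
- A reader might infer that chance imbalance biases the result. It does not; the type I error and the interval already allow for it.
- A reader might take a particular gain, such as 88% power, as established. It needs R² = 0.20, which nothing in the protocol supports.
- A reader might think that adjustment repairs the primary analysis. At present no interval is compared with the margin at all. A chi-square or Fisher test at p < 0.05 tests for a difference and not for non-inferiority, so the gain in power depends on that separate repair.

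**Conclusion.** The point holds as a low-cost improvement. The only analysis that reaches treatment failure is unadjusted, no stratification is stated, and three plausible baseline predictors are on the case record form.

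The unadjusted analysis remains valid; what may be lost is precision. Under assumed R² values of 0.02 to 0.20, power at p = 0.50 and margin 0.16 goes from 80.2% to between 81.0% and 88.1%, a gain of about 1 to 8 percentage points. The lower end is as plausible from the protocol as the upper. If failure is well below 50%, the gain appears mainly as a narrower interval.

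These figures assume that the primary result is a risk difference compared with 0.16, which the Data analysis plan does not yet provide.

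**What to change.** In the Data analysis plan, before outcome data are seen (which matters all the more in an open-label trial):

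- Make the primary estimate the risk difference in treatment failure, amoxicillin minus ampicillin, adjusted for age (item 6), admission SpO2 (item 90) and weight-for-length/height Z-score (item 55), each as a continuous value. Do not use severe-malnutrition status as the covariate, because Annex 3 defines it only for 6–59 months while enrolment starts at about 2 months.
- Obtain it by standardisation after logistic regression or by linear regression with robust standard errors. Either keeps the estimate on the scale of the margin; a conditional odds ratio would not.
- Compare the two-sided 95% upper limit with 0.16. This is needed whether or not covariates are used.
- Keep the unadjusted risk difference as a sensitivity analysis.

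The cost is a sentence or two in the analysis plan and agreement on the covariate list. No new data and no additional children are needed.
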